## Abstract

**Background:**

This study is born from a partnership between Web editors of *Naître et grandir* (N&G) and *AboutKidsHealth* (AKH) and researchers who developed and validated the Information Assessment Method (IAM). N&G and AKH are popular Canadian websites with high-quality comprehensive information about child development, education, health, and well-being. IAM allows parents to assess online information and provide feedback to Web editors. High-quality online consumer health information improves knowledge, self-efficacy, and health. However, low-socioeconomic status (SES) parents underuse N&G and IAM, despite these parents being more likely to report decreased worries and increased confidence as outcomes from N&G information.

**Objective:**

The study is aimed to improve low-SES parents’ use of online child information and interaction with Web editors and explore subsequent health outcomes for parents and children.

**Methods:**

Multiphase mixed-methods design. Our general approach is centered on organizational participatory research. In phase 1, we will conduct a qualitative interpretive study to identify barriers and facilitators to using N&G information and to interacting with N&G editors via IAM; interview more than 10 low-SES parents about their experience with N&G and IAM and more than 10 nonusers of N&G and IAM; and use thematic analysis to identify main barriers and facilitators. In phase 2, we will integrate parents’ views (phase 1 findings) in N&G and IAM and implement a new version: IAM+N&G+. In phase 3, we will conduct a quantitative prospective longitudinal study (pre-/postimplementation monitoring of knowledge use and outcomes). We will compare the use of original (IAM and N&G) and new (IAM+ and N&G+) versions using Google Analytics variables, IAM variables, a material and social deprivation index, and demographics. We anticipate increased use post implementation (linear mixed modeling). In phase 4, we will conduct a qualitative descriptive study on outcomes of information use. We will interview more than 30 low-SES parents who receive and rate the N&G+ newsletter using IAM+ and analyze data in the form of life histories to describe how parents and children experience perceived outcomes.

**Results:**

The project was funded in 2017 by the Canadian Institutes of Health Research and received an ethics approval by the McGill University’s institutional review board. Data collection for phase 1 was completed in 2018. Phases 2 to 4 will be conducted until 2020. Findings from this study will also be used to develop a free toolkit, useful to all Web editors, with recommendations for improving health information for low-SES persons and interactions with them using IAM.

**Conclusions:**

The results of this study will provide a deep understanding of how low-SES parents use online child information and interact with Web editors. Following the implementation of IAM+N&G+, results will also elucidate subsequent health outcomes for low-SES parents and children after interaction with Web editors has been optimized.

**International Registered Report Identifier (IRRID):**

PRR1-10.2196/9996

## Introduction

### Rationale

Early life experience is a determinant of social inequalities in physical, mental, and social well-being [1-6]. Children living in poverty are more likely to suffer from developmental and health problems, and childhood interventions can decrease incidence and prevalence of these problems [7-12]. The proposed project is aimed to assess and improve a childhood intervention: the *Naître et grandir* (N&G) website and newsletter on child development, education, health, and well-being, which includes the Information Assessment Method (IAM) that allows N&G readers to continuously assess, and subsequently the N&G editors to improve, the content shared on the N&G website and newsletter.

Parents with low education and low income, hereafter referred to as parents with low socioeconomic status (SES), typically have a low literacy level (limited ability to acquire, understand, evaluate, and use written information). Low parental literacy level is particularly detrimental to child health: a low literacy level is associated with worse health status, difficulties accessing health care, and poorer preventive health behavior and self-management of health problems [13-23].

Education and income are the most important SES indicators, and together, they are strongly associated with child health status [24,25]. According to research on information-seeking behavior, parents with low SES have greater information needs than parents with high SES [26]. The use of high-quality online information can improve quality of life and have positive family, economic, and social impacts on low-SES parents, including refugee and homeless parents [27-31]. High-quality information and literacy-related interventions can reduce unnecessary calls and visits to health professionals, increase knowledge and self-efficacy, and improve health [16-19,32-47].

N&G [48] is a website independent from industry funding that provides high-quality information (based on research syntheses and validated by experts) on child development, education, health, and well-being. N&G users can access hundreds of information pages (1 page per topic) that are organized in age group categories, ranging from pregnancy to the age of 8 years. N&G also produces a weekly newsletter to support parents, including those with a low literacy level, having children under the age of 8 years.

N&G partnered with investigators from McGill University to validate and implement the IAM to continuously assess and improve content shared on the N&G website and newsletter [49-53]. In line with the Canadian Institutes of Health Research (CIHR)’s definitions [54], the IAM is a knowledge translation tool for monitoring N&G information use, and its impact on parents is measured by expected health/well-being benefits. It is also fostering parent engagement by enabling parents to interact with N&G editors by providing feedback on the information content. The IAM questionnaire includes 7 questions (with clickable answers and 2 comment boxes), allowing users to rate on the situational relevance, cognitive/affective impact, intention to use and expected benefits of specific information content (N&G information page), and write comments.

During our pilot phase (September 1, 2014, to August 31, 2016), we collected 34,021 IAM ratings (completed IAM questionnaires) from parents, relatives, and professionals (education, health, and social services) who read N&G content. In line with studies on social inequalities in Web information use [55-61], the statistical analysis of these ratings revealed a social gradient: low-SES parents underuse N&G and the IAM (Figure 1). Results also indicated that low-SES parents are more likely to report decreased worries and increased confidence as a result of using N&G information [50]. There is a need to understand this gradient to improve N&G content and reach low-SES parents and a need to explore how the use of knowledge translates into health and well-being outcomes for low-SES parents and children.

**Figure 1 figure1:**
[figure not shown]
Social gradient in assessing *Naître et grandir* (N&G) information with Information Assessment Method (IAM). A dot represents the total number of IAM ratings completed by all N&G newsletter subscribers living within the postal code areas of a Canadian centile of Material Deprivation. There is a negative linear relationship as areas with higher deprivation have a lower proportion of newsletter ratings/subscribers. The correlation coefficient is −.42 (*P*<.001).

### Goal and Objectives

This study (research protocol) has been recently funded by CIHR. As per CIHR’s definition of knowledge translation (“making people aware of knowledge and facilitating knowledge use to improve health”) [62], our goal is to improve how low-SES parents engage with and use online information about child development, education, health, and well-being; learn how this format for knowledge sharing translates to improved health and well-being outcomes for low-SES parents and their children; and explore their interaction with Web editors to influence content (responsible for websites’ content). On the basis of the N&G team's (the director and 2 coordinators) questions and using the Knowledge-to-Action framework [63], we determined 4 research objectives:

Objective 1: Identify low-SES parents’ views on barriers and facilitators to accessing, understanding, and using N&G information content and to interacting with N&G editors via the IAM.Objective 2: Adapt N&G content/functions and the IAM tool (user-centered design) to reduce barriers and optimize facilitators identified in phase 1 and implement new versions labeled N&G+ and IAM+.Objective 3: Evaluate whether N&G+ and IAM+ result in a higher proportion of low-SES parents engaging with the N&G site and the content provided and interacting with editors via the IAM.Objective 4: Describe how expected health and well-being benefits of N&G+ information use (reported via IAM+) are experienced by parents with low SES and their children.

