##### Measurement

N&G and McGill already use Google Analytics, an objective and reliable automatic data collection of N&G readers’ demographic characteristics and website use behavior (based on javascript codes in each Web page) [117-120]. IAM raters’ demographic data are collected with a questionnaire (linked to an anonymized identifier). The validated IAM questionnaire [53] collects self-reported information use and subsequent expected health/well-being benefits for parents and their child.

**Table 2 table2:** Types of outcomes monitored weekly.

Type	Outcome	Description and data source
A1	N&G^a^ sessions	Weekly number of unique sessions (Google Analytics)
A2	N&G read	Weekly proportion of sessions with at least 1 page entirely read (Google Analytics)
A3	IAM^b^ ratings	Weekly number of IAM questionnaires submitted
B1	N&G mediated	Weekly proportion of IAM ratings information used for the child of someone else
B2	N&G used	Weekly proportion of IAM ratings information used for oneself and one’s child
C	Expected benefits	Weekly proportion of IAM ratings expected health or well-being benefit for a parent and child, including at least 1 of the following self-perceived benefits (IAM choices of response): improvement of the health or well-being of a child, being less worried, prevention of a problem or the worsening of a problem, handling a problem, and being more confident to decide something with someone else

^a^N&G: *Naître et grandir*.

^b^IAM: Information Assessment Method.

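### Objective 3 asks what proportion of low-SES parents engage, but every Phase 3 outcome counts sessions or ratings, so more use per parent could be misread as more parents

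*Protocol article*

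**What the plan says.** The Goal and Objectives section states Objective 3 as a question about people: do the new versions "result in a higher proportion of low-SES parents engaging with the N&G site"? The same sentence asks this of contact with the editors through the questionnaire.

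Table 2 (Phase 3, Measurement) fixes the outcomes that are to answer it:

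- A1: "Weekly number of unique sessions (Google Analytics"
- A2: "Weekly proportion of sessions with at least 1 page entirely read (Google Analytics"
- A3: "Weekly number of IAM questionnaires submitted"
- B1: "Weekly proportion of IAM ratings information used for the child of someone else"; B2 and C likewise take IAM ratings as their denominator.

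Under Phase 3, Setting, a session closes after 30 minutes without activity, and a relative on the same IP address can fall within it. Under Covariates, the deprivation index is attached to each session. The Measurement text also says that "IAM raters’ demographic data are collected with a questionnaire (linked to an anonymized identifier"), but no listed outcome uses that identifier to count raters.

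Elsewhere the article speaks of volume. The Abstract and the Phase 3 Anticipated Results predict more use, and the Discussion, in the section on direct impact, glosses engagement as a count of visits.

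**The concern.** The objective and its outcomes have different units. One parent can open several sessions and submit several questionnaires in a week, so A1 and A3 mix two things: how many low-SES parents take part, and how often each does. Phase 2 changes the site and the questionnaire to remove barriers, and either quantity may move as a result.

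At stake is the answer to Objective 3 in the terms in which it is stated. A larger count in the most deprived quintile could be taken to show that more low-SES parents engage when their number has not changed or has fallen. A flat count could equally conceal a gain. This is separate from secular trend or background traffic: perfect control of both would leave the ambiguity in place.

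**Working it through.** The plan gives no figure to reproduce here. Study Size anticipates about 5 million sessions and 15,000 ratings per period, with no number of users or raters. The check compares units and then applies one identity.

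**1. Units against the objective**

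| Quantity | Counted | Denominator |
|---|---|---|
| Objective 3 | low-SES parents who engage | low-SES parents |
| A1 | sessions | none |
| A2 | sessions with a page fully read | sessions |
| A3 | questionnaires | none |
| B1, B2, C | ratings with the stated answer | ratings |

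No row below the first has parents as numerator or denominator.

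**2. Identity**

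Events = persons × events per person, so relative change in events = (1 + change in persons) × (1 + change in frequency) − 1.

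**3. Numbers**

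The one stated frequency is in Table 3, footnote c: an average of 1.3 consultations per week among Quebec parents. It is not specific to low-SES parents and is used only as a starting value. All changes below are assumptions.

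- Parents fixed, visits up from 1.3 to 1.43, 1.6 or 1.95 per week: 1.43/1.3 = 1.10, 1.6/1.3 = 1.23, 1.95/1.3 = 1.50. A1 rises 10%, 23% or 50% with no additional parent.
- Parents down 10%, frequency up 25%: 0.90 × 1.25 = 1.125. The count rises 12.5% while fewer parents take part.
- Parents up 10%, frequency down 10%: 1.10 × 0.90 = 0.99. The count falls 1% despite a real gain.
- Raters up 20%, ratings per rater down 17%: 1.20 × 0.83 = 0.996. A3 is flat.

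**4. Does anything else in the plan separate the two factors?**

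- Statistical Analysis provides for clustering and random effects. These handle dependence between records; they do not turn a count of events into a proportion of parents.
- The interaction of quintile with pre/post status is fitted to these same outcomes, so it inherits their units.
- Timeline and Potential Challenges relies on proportions to deal with historical events. A1 and A3 are raw counts, and the proportions that are used have sessions or ratings beneath them.

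**5. Is a person-based measure within reach?**

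For the IAM, largely yes. An anonymized identifier exists, the Timeline section reports that monthly rater numbers were stable in the pilot (so raters have been counted), and Figure 1 shows that subscriber denominators by deprivation area exist. For the site, only in part: web-analytics users are split across devices, and no denominator of low-SES parents is given.

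**The case against.** The strongest reply is that the article itself defines engagement as visits. The Abstract, the Phase 3 heading and the Anticipated Results all speak of use, and A1 and A3 measure use. On that reading, heavier use by existing low-SES parents is a success, and the fault is one loosely worded sentence. Much of this stands: it makes rewording a legitimate remedy for the site. It does not remove the conflict, because Objective 3 as written asks for a proportion of parents.

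Several stronger readings are tempting but unsupported:

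- A reader might infer that Phase 3 will report a count increase as wider reach. No Phase 3 passage promises to report numbers of parents; the most that can be said is that the counts could be misread.
- A reader might infer that existing low-SES users are few. Table 3, footnote c, says that 76% of Quebec parents of children under 8 consult the site; the low-SES share is not given.
- A reader might take Figure 1 as a person-based pilot measure. Its legend says "areas with higher deprivation have a lower proportion of newsletter ratings/subscribers", so the numerator is ratings, as in A3. Only the denominator can be borrowed.
- A reader might assume that an easier questionnaire will mainly raise ratings per existing rater. The article gives no ground for that; it could equally bring in first-time raters.
- A reader might turn weekly ratings into weekly parents. The pilot gives 34,021/104/5 ≈ 65 ratings per week per quintile and the Phase 3 projection 15,000/39/5 ≈ 77, both assuming equal shares. Neither is a ceiling or a number of parents: ratings per rater is nowhere stated, and pilot raters included relatives and professionals.

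**Conclusion.** The concern holds as a mismatch of units. Followed as written, Phase 3 cannot tell more low-SES parents from more use per parent, so Objective 3 is not answered in its own terms. The mismatch covers all six outcomes; A1 and A3 are where misreading is most likely.

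The conclusion rests on the definitions in Table 2 and on the identity above, not on any assumed effect. The size of a possible error cannot be estimated from the article, because users, raters and ratings per rater are not given. The 23% rise and the flat A3 are illustrations under assumed changes. The article does not show that a wrong conclusion will be drawn, and its passages on volume of use mean that part of the repair is to reconcile the text. This should be corrected, and the IAM part is cheap to correct.

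**What to change.** **IAM part of Objective 3.** Add, as the measure that answers it, the number of distinct IAM raters per deprivation quintile and period, counted by the anonymized identifier. For ratings that come from the newsletter, divide by newsletter subscribers in that quintile. Keep A3, and add ratings per rater, as measures of intensity.

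**Site part.** Report distinct web-analytics users per quintile beside A1 as supportive only. Limit the conclusion from A1 to volume of use, and reword that part of Objective 3 to match, so that it agrees with the Abstract, the Anticipated Results and the Discussion.

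**Cost.** A little extra derivation. The rater count depends on the identifier persisting across a rater's submissions, which the article does not state and which should be confirmed first. The subscriber-based proportion covers newsletter raters only and says nothing about parents who do not subscribe. Quintile remains an area measure, and raters may include people other than parents, so the new measure comes closer to Objective 3 without matching it exactly.

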### Systematic Literature Review and Theoretical Model

The nominated principal investigator (NPI) led a CIHR-funded systematic review and proposed a comprehensive harmonized typology of (1) outcomes associated with the use of online consumer health information and (2) conditions (network and resources) leading to these outcomes [64-67]. A total of 68 studies were analyzed using framework synthesis [68,69]. This synthesis was based on an initial framework derived from information studies [49,70-78] and led to propose an innovative theoretical model (Figure 2) [66,67]. This model includes positive and negative health outcomes of online consumer health information in a primary care context and is (information) consumer oriented.

The model comprises 13 main concepts (42 factors and outcomes) and will be used in this study to inform data collection and analysis, for example, the phase 1 qualitative interview guide and interpretive thematic analysis. The model will contribute to establish a chain of evidence linking ultimate outcomes of information (such as health outcomes), intermediary outcomes (such as cognitive impact of information), and conditions associated with outcomes (information needs and seeking behaviors and contextual factors).

**Figure 2 figure2:**
[figure not shown]
Theoretical model.

#### Outcomes

The model includes an organizational level of information outcome (eg, increased or decreased use of health services) and 4 individual levels of outcomes of information. The latter outcomes reflect how information is valuable from the consumer’s perspective: situational relevance, cognitive impact, use of information (conceptual, legitimating, instrumental, and symbolic use), and subsequent health and well-being outcomes.

#### Conditions

The model includes conditions associated with outcomes of information in relation to a specific situation: a particular information object is acquired or delivered (eg, a Web page or a newsletter) in a particular situation (eg, before or during or after an encounter with someone) directly or with help from a relative or a professional. The main conditions are information needs and seeking behaviors; individual characteristics (such as electronic health literacy); social and technical factors (such as social networks); relationships with professionals (such as teachers, clinicians, and social workers); and access to education, health, and social services. The first phase of this study will specifically look into conditions experienced by low-SES parents, such as media competence.

Direct acquisition of online information depends on an impetus to search (motivation), momentary internet connection, internet search skills, and one’s ability to understand the content that may or may not be adapted to their individual literacy level [79-81]. Approximately 95% of parents of preschool children have direct individual access to the internet in Quebec [61], and parents can also access it at office workplaces and public libraries [79-81]. Literacy level is generally defined as the degree to which a person has the ability to “acquire, understand, evaluate, and use information” needed to obtain services and make appropriate decisions [23]. Computer literacy, information literacy, and health literacy are interdependent (eg, a person with a low literacy level has a low level of health literacy). Culture is central in literacy, and one’s literacy level depends on one’s ability to understand systems of symbols from one’s own culture or a dominant culture and language, for example, immigrants and refugees may have a higher literacy level in their country of origin compared with their adoptive country [23]. As mentioned in our model, the literacy level is *situational* and *contextual*, given that a social network can compensate for an individual’s low literacy level.

Mediated (by someone else) acquisition of information is very common. The absence of an individual connection 24/7 is no longer the primary barrier to seeking health information [80]; for example, our pilot data show that 18.1% of IAM ratings concerned N&G information seeking for someone else’s child (eg, relative’s, friend’s, neighbor’s, or client’s child). Even homeless parents or recent immigrants and refugees can acquire online consumer health information directly or mediated by their social network, including community organizations; public libraries; and education, health, and social services [23,27-31]. Indeed, information studies show that consumers combine mediated information with direct acquisition of online health information, the latter allowing them to probe information provided by professionals [64-67]. For analytical purpose, we conceive these combinations as the interpenetration of social systems centered on communicative action, for example, the health system (mediated access) and a consumer parent system (direct access and mediated access via their social network) [82-85].

